## Methods

This study follows a repeated measures observational design with baseline assessments, repeated measures over the course of treatment and post-treatment assessments. Twelve to sixteen sessions of NET will be provided to all patients included in the study. Various questionnaires will be administered at baseline (T0, pre-treatment), 1 week after NET completion (T1, post-treatment) and 6 weeks after NET completion (T2, follow-up). In addition, assessments to measure potential processes of change will be performed at the start of each NET session. See Fig. 1 for a detailed overview of the planned design and administered measures.

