In the present paper, the feasibility, rationale and protocol of an ongoing trial are described. Specifically, we aim to identify relevant predictors of PTSD symptom change during and after NET in 80 displaced victims of interpersonal violence. The primary hypotheses of the study are (1) it is feasible to administer highly repeated measures, within a diverse group of displaced persons. (2) High perceived daily stress, emotion dysregulation, and low mood at baseline and during NET predict higher drop-out, higher no-show and poorer treatment response of NET (i.e. less PTSD symptom reduction), thus undermining the feasibility of NET; (3) Reduction in perceived daily stress and improvement in emotion regulation and mood during NET are associated with concurrent reductions in PTSD symptoms during NET; (4) Change in perceived daily stress, emotion dysregulation, and mood during NET predict subsequent changes in PTSD symptoms at later stages of NET. Furthermore, the study aims to establish whether NET contributes to positive aspects of mental health.

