#### Discontinuation of the intervention and drop-out

Discontinuation of NET will take place if patients so wish or if multi-disciplinary clinical evaluation indicates that continuation is not in the best interest of the patient. If patients wish to stop participating in the study but wish to continue NET, this will be allowed. Patients will be considered dropouts when there are deviations from the NET treatment protocol for more than four consecutive sessions (i.e. no trauma-focused approach during the sessions or no-show), since in these cases the effectiveness of the treatment offered cannot be assured [34].

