#### PTSD Checklist for DSM-5 (PCL-5)—administered pre-and post-treatment

The 20 item PCL-5 is a self-report checklist which measures the presence and severity of the 20 DSM-5 symptoms of PTSD on a 5-point scale (0–4) (e.g. ‘Trouble remembering important parts of the stressful experience’)*.* Mean scores will be calculated, ranging from 0 to 4. It will be used to indicate PTSD symptom severity pre- and post-treatment. Administration of the questionnaire takes approximately 10 min. The instrument has good psychometric quality [42].

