#### Primary Care Post-traumatic Stress Disorder (PCPTSD)—administered before each session

Because a short version of the PCL-5 is unavailable, the five-item Primary Care Post-traumatic Stress Disorder (PCPTSD) checklist was selected to increase the feasibility of the frequently repeated measurements. This questionnaire is used to measure PTSD symptoms [43]. For the purpose of this study the indicated timespan was changed from ‘In the past month, have you’ to ‘In the last week’ to match the other pre-session measures for possible predictors. An example item is: ‘In the last week did you have nightmares about the event(s) or thoughts about the event(s) when you did not want to?’ These items will be scored on a VAS-scale ranging from 0 (not at all) to 100 (extremely). The questionnaire has good psychometric qualities [41]. Mean scores will be calculated, ranging from 0 to 100.

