### Data collection, management and analysis

#### Procedure pre-session measures

During baseline (T0) and at the start of each TFT session, the patient’s fixed practitioner or a supervised master’s level psychology student will administer the thirteen items selected to assess the four abovementioned possible predictors. To avoid an order effect, the sequence of the measures for possible predictors and the order of questions within every measure will change with every session. These measures will only be administered during the treatment period. They will be administered by pen and paper and are expected to take on average 10 min. Questionnaires are translated from their original English version according a forward-backward procedure by two independent native speakers into Dutch, and by professional translators into Arabic, French, Amharic and Tigrinya. Interpreters will assist for other languages.

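### T1 and T2 are timed only from NET completion, so patients who stop early have no scheduled post-treatment PCL-5 or QPR, and the response regression is likely to lose them

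*Protocol article*

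**What the plan says.** The Methods section of the protocol article schedules the post-baseline questionnaires at "1 week after NET completion (T1, post-treatment) and 6 weeks after NET completion (T2, follow-up". No calendar date or other anchor is given.

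The section on discontinuation and drop-out foresees early stopping: "Discontinuation of NET will take place if patients so wish", or when clinical evaluation advises against continuing. It adds a definition: "Patients will be considered dropouts when there are deviations from the NET treatment protocol for more than four consecutive sessions". It covers patients who leave the study but continue NET. It gives no assessment time for patients who leave NET.

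Two PTSD measures are used. For the PCL-5 the article says: "It will be used to indicate PTSD symptom severity pre- and post-treatment". For use during treatment, the "five-item Primary Care Post-traumatic Stress Disorder (PCPTSD) checklist was selected to increase the feasibility of the frequently repeated measurements". The section on pre-session measures places that short set at T0 and at each session, and adds: "These measures will only be administered during the treatment period".

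Hypothesis 2 (Background) states that high stress, emotion dysregulation and low mood "predict higher drop-out, higher no-show and poorer treatment response of NET (i.e. less PTSD symptom reduction"). The Statistical analysis section examines the baseline part of this with multiple and logistic regression. It reserves multilevel models for the session-level questions.

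**The concern.** A patient who never completes NET never reaches T1 or T2 as these are defined, and the session measures end with treatment. An ordinary regression of PCL-5 response needs a post-treatment value, so following the schedule leaves early stoppers out of it.

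In this study the loss is not incidental. Hypothesis 2 makes drop-out and poorer response joint consequences of the same predictors, so the patients left in the regression would be selected on one hypothesised effect while the other is estimated. The Background itself warns that completion can be low in this population.

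The result also has a practical use. The Discussion says that if these factors turn out not to predict the course of PTSD, clinicians might be encouraged to offer trauma-focused therapy despite them. A slope that is attenuated or imprecise because patients were lost could feed that conclusion.

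**Working it through.** **1. Which data does an early stopper have?** The pre-session set has thirteen items: PSS 4 + DERS impulsivity 3 + PCPTSD 5 + mood 1 = 13. So PCPTSD is collected at T0 and at every attended session. The early stopper has PCL-5 and QPR at T0 and PCPTSD up to the last attended session, but no scheduled PCL-5 or QPR afterwards.

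**2. Reference for N = 80.** The Participants section says 80 patients allow medium to small effects to be detected. It gives no alpha, power, effect size or test, so the figure cannot be reproduced. Assuming two-sided alpha 0.05 and 80% power, the smallest detectable correlation is r = tanh[(1.960 + 0.842)/√(n − 3)]. For n = 80 this is tanh(2.802/8.775) = 0.309. Power for r = 0.30 is Φ(0.3095 × 8.775 − 1.960) = Φ(0.756) = 77.5%.

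**3. Precision if only completers have T1/T2.** Drop-out rates are assumed; n = 80 × (1 − rate).

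| Drop-out | n with outcome | Detectable r | Enrolment needed for 80 outcomes, 80/(1 − rate) |
|---|---|---|---|
| 10% | 72 | 0.325 | 89 |
| 20% | 64 | 0.344 | 100 |
| 30% | 56 | 0.367 | 115 |
| 40% | 48 | 0.395 | 134 |

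If drop-out depends on the predictor only (log-odds 0.5 per SD), the predictor's range narrows slightly and the completers' correlation is 0.295 at 20% and 0.293 at 40% drop-out. Power is then 66% and 53%, against 77.5% with all 80 outcomes.

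**4. Bias.** Simulation with 1,000,000 draws. X is the standardised predictor and Y the standardised PTSD outcome (higher = worse), with Y = 0.30X + √(1 − 0.30²)·e. Drop-out follows logit P = a + gₓX + g_yY, with a = −1.2 or −0.7. The slope of Y on X is fitted in completers.

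| gₓ | g_y | Meaning | Drop-out | Completers' slope |
|---|---|---|---|---|
| 0.5 or 0.8 | 0 | predictor only | 24-35% | 0.30 |
| 0.3 | 0.3 | worse-off leave, weak | 24-34% | 0.28 |
| 0.5 | 0.5 | worse-off leave | 26-35% | 0.25-0.24 |
| 0.8 | 0.8 | worse-off leave, stronger | 29-37% | 0.20-0.19 |
| 0.5 | −0.5 | better-off leave | 25-34% | 0.32-0.33 |
| 0.8 | −0.8 | better-off leave, stronger | 27-36% | 0.36-0.37 |

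The first row is expected: selection on X alone leaves the mean of Y given X unchanged. In the worse-off rows at 0.5 to 0.8, the slope loses between 1 − 0.25/0.30 = 17% and 1 − 0.19/0.30 = 37%, and the completers' mean outcome looks 0.15 to 0.29 SD better than that of all starters. In the better-off rows both effects reverse.

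**The case against.** Three stronger readings are tempting, and the document supports none of them.

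- *Drop-outs have no PTSD outcome.* They have PCPTSD at T0 and at each attended session. The multilevel models for hypotheses 3 and 4 can use incomplete series, so the gap concerns the PCL-5 regression for hypothesis 2 and the QPR.
- *The analysis is completers-only.* The article states no such restriction and no deletion of missing cases. The analysis set and missing-data handling may be in a full protocol or SAP, and the design figure is not shown. Nor is drop-out the same as non-completion: patients who attend but have more than four consecutive sessions without trauma focus count as drop-outs and could still reach T1.
- *The slope is biased towards zero.* Hypothesis 2 supplies only the link from predictor to drop-out, and that link alone produces no slope bias. The second link, from PTSD course to drop-out given the predictors, is plausible because stopping follows the patient's wish or a clinical evaluation, but the article does not establish it. Its sign could go either way.

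It is also fair to say that drop-out and no-show are analysed as outcomes in their own right, so a predictor that drives patients out can be detected there, and that the Discussion concedes reduced internal validity.

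All of this stands and limits the point. It does not remove it: the visit rule is stated in the article, and an analysis plan can handle missing values but cannot afterwards create an assessment that was never scheduled.

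**Conclusion.** The point holds in a limited form and should be fixed. As written, T1 and T2 are undefined for patients who stop NET early, and the PCL-5 response regression is likely to lose them in a way that hypothesis 2 expects to be related to the predictors.

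The certain cost is precision: at assumed drop-out of 20-40%, the detectable correlation rises from 0.309 to between 0.344 and 0.395. Bias is conditional. From a true slope of 0.30, the scenarios range from none, through attenuation to 0.25-0.19, to inflation to about 0.33 (0.36-0.37 under the stronger reverse dependence). Drop-out rates, strengths of dependence, alpha and power are all assumptions. The document fixes neither the direction nor the size of any bias.

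**What to change.** 1. Define T1 and T2 for everyone who starts NET. For early stoppers, anchor them to a fixed interval after the last attended session or to the planned end date of NET, and collect at least the PCL-5.
2. Base the baseline-predictor response analysis on all starters: a mixed model of the per-session PCPTSD scores with a predictor-by-time term, and a separate longitudinal model of PCL-5 at T0, T1 and T2. Keep the two apart because the scales differ (0-100 and 0-4).
3. Report the completers-only regression as a sensitivity analysis.

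The models use data already being collected. They rest on drop-out being explained by what was observed before it, which is why the extra PCL-5 assessment is worth having as well.

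The cost is a short amendment and some extra contact attempts, and not all early stoppers will attend. At the time of writing, the article reports that enrolment was continuing and no analysis had been done, so the change was still open. Post-treatment assessments already missed cannot be recovered.

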**Fig. 1 Fig1:**
[figure not shown]
Design and overview of planned assessments. Note*:* Biographical data: gender, age, residence status, etc.; ETI, Early Trauma Inventory- Short Form; DERS-18, Difficulties in Emotion Regulation Scale-Short Version; LEC-5, Life Events Checklist for DSM-5; PCL-5, Post-traumatic Stress Disorder Checklist for DSM-5; PCPTSD, Primary Care Post-traumatic Stress Disorder; PSS, Perceived Stress Scale; QPR-15, Questionnaire on Process of Recovery-Short Version

NET will be provided by trained psychologists, psychotherapists, medical doctors and psychiatrists. Psychologists and master’s level psychology students will perform assessments for the study. All involved professionals have extensive experience in working with migrants (in a culturally sensitive manner) and interpreters.

### Participants

The study will take place at an outpatient clinic specialized in mental health care for refugees, asylum seekers, victims of sexual exploitation and otherwise traumatized populations in the Capital region in the Netherlands. The study aims to include 80 participants, in order to detect medium to small effect sizes [35]. Patients are referred to the clinic by a general practitioner or by a partnering social welfare organization. Patients’ background/nationality is diverse; most originate from West Africa, the Middle East and Eastern Europe. Their legal status varies from having obtained a residence permit or even Dutch citizenship to illegal residence in the country, and they may reside in asylum seekers centres, specialized shelters for victims of sexual exploitation, governmental shelters for illegal persons or live independently.

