## Background

Worldwide, there is an increase in the number of victims of interpersonal violence who are forced to leave their home country [1]. When entering a host country, these displaced persons are usually referred to as either ‘refugees’, ‘asylum seekers’, ‘trafficked human beings’, ‘illegal immigrants’ or ‘undocumented people’, depending on their trauma background and legal status. Mostly these groups overlap in their experience of forced migration, their marginalized social position, and the challenges they encounter. In this paper, we will therefore collectively refer to all such groups as ‘displaced people’.

As a result of assorted traumatic events, like war- and conflict-related violence, sexual violence and exploitation, many of these displaced people suffer from a post-traumatic stress disorder (PTSD) [2–5]. PTSD symptoms cause a great burden, render people unable to engage in daily activities and put them at risk for re-victimization [6]. Displaced people suffering from PTSD could therefore benefit from trauma-focused therapy (TFT). TFT is a psychological intervention aiming to decrease PTSD symptoms by fostering the processing of traumatic memories.

Scientific research into TFT for displaced people is scarce. Studies into TFT for non-refugee traumatized populations show higher effects (*d* = 1.08–1.40) [7], than for refugee populations (*g* = .25–1.01) [8]. Moreover, the feasibility of evidence-based therapies within the refugee population is complicated by post-migration obstacles [9] which can result in low treatment compliance and completion levels. Most likely, the primary focus on PTSD fails to address the broader challenges faced by displaced people [10]. Therefore, more insight is needed into factors affecting treatment response during TFT and conditions for recovery. Identifying factors that undermine the feasibility of TFT for displaced people may help to refine the timing and focus of interventions, and thus improve treatment response.

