### Statistical analysis

First, multiple regression analyses and logistic regression analyses will be performed to examine whether high perceived daily stress, emotion dysregulation and low mood at baseline predict drop-out, no-show and treatment outcomes. Secondly, the concurrent association between each possible predictor measured prior to each session (i.e. perceived daily stress, emotion regulation and mood) and PTSD symptoms will be examined using bivariate (multilevel) growth modelling, as multiple observations of the predictor variables and PTSD symptoms (level 1) are nested within individuals (level 2) [49]. In order to infer that change in the predictor variables leads to change in PTSD symptoms, we will examine the timeline (i.e. temporal precedence) in two ways [50, 51]. The dynamic (i.e. temporal) associations will be examined by estimating whether change in PTSD symptoms from the previous week to the current week (t) can be predicted by change of a possible predictor at the previous week (t-1) using multilevel modelling. To examine the timeline of larger shifts instead of week-to-week changes, it will be examined whether the earliest significant decrease in mean levels of each possible predictor (improvement) occurs before the largest reduction in mean levels of PTSD symptoms.

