Evidently, there are factors possibly impacting treatment response. For the purpose of this study, repeated measures were selected on the basis of relevant studies [41, 44] and clinical insights. Thus, the set of questions have been tailored to the specific characteristics of the study population. Conclusions drawn from the study therefore may hold relevant implications in clinical practice for displaced victims of interpersonal violence. Although the chosen subscales support the clinical validity of the study, the PTSD and emotion dysregulation subscales have not been validated as weekly repeated measures.

It is important to note that inclusion for the current study has already started; however, it is planned to run until early 2021. Critically, no data analysis has currently been performed yet.

We expect that the findings of this study will contribute to both the scientific and the clinical field. Identifying factors that limit treatment response may in turn inform the development of improved treatment modules that specifically address these blockages. The promotion of self-efficacy or problem-solving skills prior to NET, for example, may decrease perceived daily stress and its constraining effect on the feasibility of NET. Likewise, promoting emotion regulation prior to NET may intensify its potential supportive role for TFT. Additionally, if these factors have no predictive value for the course of PTSD during treatment, clinicians might be encouraged to offer TFT to patients despite the presence of daily stressors, emotion regulation difficulties and mood problems. By identifying predictors of treatment response, the current study can enable treatment indications to be tailored to individual characteristics.

Furthermore, exploring these predictors sheds a broader light on the consequences of trauma, beyond a narrow focus on PTSD, and may provide clues for a wider range of relevant treatment foci. In this way, this study responds to the ongoing debate on the emphasis focus of PTSD in designing treatments for displaced populations [10].

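### The sensitivity claim for N=80 has no stated scope; its small-effect end fails for the baseline-prediction regressions, although it is plausible for the session-level models

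*Protocol article*

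**What the plan says.** In the Participants section, the sample size rests on one sentence and a citation: "The study aims to include 80 participants, in order to detect medium to small effect sizes". No test, effect metric, alpha or power is named, and the sentence is not limited to any analysis.

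The second primary hypothesis, at the end of the Background, reads: "High perceived daily stress, emotion dysregulation, and low mood at baseline and during NET predict higher drop-out, higher no-show and poorer treatment response". It therefore has a baseline part and a during-treatment part.

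The Statistical analysis section covers the baseline part first: "multiple regression analyses and logistic regression analyses will be performed to examine whether high perceived daily stress, emotion dysregulation and low mood at baseline" will "predict drop-out, no-show and treatment outcomes". It then turns to multilevel models of the measurements taken before each session. The Methods section plans 12 to 16 sessions per patient.

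The Discussion considers what a null finding would mean: "if these factors have no predictive value for the course of PTSD during treatment, clinicians might be encouraged to offer TFT to patients" who have daily stressors, emotion regulation difficulties or mood problems.

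**The concern.** The plan contains two kinds of analysis with very different information. In the session-level models, each patient contributes many observations. In the baseline regressions, each patient contributes one value of each predictor and one outcome, so the repeated measurements add nothing and the sample size is at most 80. One sensitivity statement cannot cover both.

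What is at stake is how a null baseline result is read. A reader who takes the Participants sentence at face value would think that a baseline predictor with a small effect had a good chance of being found, and that a non-significant result argues against one. If the power for such an effect is well below one half, that inference fails. It would also lend unearned support to the clinical suggestion in the Discussion.

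**Working it through.** **Inputs.** From the article: N = 80, three baseline predictors, three outcomes, 12 to 16 sessions. Assumed, because the article does not state them: two-sided alpha 0.05, 80% power, and the usual benchmarks (r = 0.10 small, 0.30 medium; f2 = 0.02 small, 0.15 medium). The sum of the normal quantiles is 1.960 + 0.842 = 2.802.

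**Can 80 be reproduced?** Not as a unique calculation. The closest match is a joint 3-df test in multiple regression with f2 = 0.15, which needs N = 77. For a small effect (f2 = 0.02), one coefficient needs about 395 patients and the joint test 550. No small-effect variant comes near 80.

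**Correlation scale (Fisher z).** Detectable r = tanh(2.802/√(n−3)).
- n = 80: tanh(2.802/8.775) = 0.31.
- Power = Φ(atanh(r)·√(n−3) − 1.96). For r = 0.10 this is Φ(0.880 − 1.960) = 14%. For r = 0.20 it is 43%, and for r = 0.30 it is 78%.

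**Multiple regression (noncentral F, λ = f2·n, n = 80, three predictors, 76 error df).**

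| Test | Power at f2 = 0.02 | Power at f2 = 0.15 | Detectable f2 |
|---|---|---|---|
| One coefficient (1 df) | 24% | 93% | 0.10 |
| All three jointly (3 df) | 15% | 82% | 0.14 |

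**Logistic regression for drop-out.** SE(log OR per SD) = 1/√(80·p·(1−p)); detectable OR = exp(2.802·SE). The drop-out rate p is assumed, and the predictors are taken as uncorrelated.

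| p | SE | Detectable OR | Power at OR 1.5 |
|---|---|---|---|
| 15% | 0.313 | 2.40 | 25% |
| 25% | 0.258 | 2.06 | 35% |
| 40% | 0.228 | 1.90 | 43% |

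Correlation among the predictors raises these thresholds. With R² = 0.3 between them, the 40% row moves from 1.90 to 2.15.

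**Loss of post-treatment data.** The article gives no rate. If 25% were lost (n = 60, purely illustrative), the detectable values become r = tanh(2.802/√57) = 0.355 and f2 = 0.14 for one coefficient.

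**What a null result leaves open.** Around an estimate of exactly zero, the 95% limits are ±tanh(1.96/√77) = ±0.22 in r. For drop-out at p = 25%, they are exp(±1.96 × 0.258) = 0.60 to 1.66. The narrowest case, p = 50%, has SE = 1/√20 = 0.224 and an upper limit of 1.55.

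**Contrast: within-person models.** Take SE² ≈ τ²/n + (1−r²)/(n(m−1)), with n = 80, m = 12 to 16 sessions, complete data, and an assumed between-patient SD of the slope τ of 0 to 0.2. The detectable within-person r is then about 0.08 to 0.12, so small effects are within reach there.

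**The case against.** The strongest reply is that the sentence contradicts no stated calculation. It stands in a condensed article, cites a source that is not at hand, and names no test. The abstract presents multilevel modelling as the analysis linking predictors to outcome, and for the session-level models the claim is plausible. That stands, and it is why the point concerns scope. That the article leaves out alpha, power and an attrition allowance is not itself a fault. What remains is a positive statement, made for the whole study, that fails for part of a primary hypothesis.

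Four stronger readings are tempting, and the documents do not support them.
- A reader might infer that the baseline tests can find only medium or larger effects. On the r scale that is about right. On the f2 scale, the single-predictor threshold of 0.10 lies below the medium mark of 0.15. Only the small end of the claim fails on both scales.
- A reader might treat the whole of hypothesis 2 as one record per patient. Only its baseline part is.
- A reader might take the Discussion as a plan to treat non-significance as reassurance. The passage is conditional, speaks of the course of PTSD during treatment, which fits the session-level analyses at least as well, and does not mention drop-out or no-show. It contains no decision rule.
- A reader might assume that only some 60 patients will have post-treatment data. The article gives no such figure. Its section on discontinuation defines drop-out by deviation from the treatment protocol and does not say that such patients go unmeasured.

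**Conclusion.** The concern holds in limited form. For the baseline-prediction regressions, the small end of the claimed range is out of reach at n = 80 even with no attrition: power is roughly one in seven to one in four, against a detectable effect of about r = 0.31, f2 = 0.10 (one predictor) or 0.14 (joint), or an odds ratio of about 1.9 to 2.4 per SD for drop-out. Any loss of outcome data raises the r and f2 thresholds.

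The result rests on two-sided 5%, 80% power and conventional benchmarks, none of which the article states. It is not sensitive to sidedness: one-sided testing gives 22% power at r = 0.10 and a detectable r of 0.28. The odds ratios also depend on the assumed drop-out rate. The sentence is therefore too broad, while the design and the session-level analyses are not called into question.

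**What to change.** Replace the single sensitivity statement by two. For example: with 80 patients, the regressions on baseline predictors can detect roughly medium effects (r about 0.3, or an odds ratio of about 2 per SD for drop-out, given the stated assumptions), with higher thresholds after expected attrition; small effects are detectable only in the within-person session analyses. The sponsor should supply the expected attrition and the assumed alpha and power, and should not take over the illustrative 25% loss.

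Report each null baseline result with its 95% confidence interval and say which effects it leaves open. Add to the Discussion that a non-significant baseline predictor alone does not support the no-predictive-value scenario.

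A formal equivalence rule with margins such as r = 0.2 or OR 1.5 should not be added. The intervals around a zero estimate (±0.22 in r, and an upper OR limit of 1.55 at best) are already wider than those margins, so the rule could never be met at this N.

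The cost is wording only: no extra patients and no change of model, but a less favourable sensitivity statement. The article says that no data had been analysed when it was written, so the restatement can be made without knowledge of results if that still holds.
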